### Sample size

The study is designed to detect a significant difference in the pre- and post-intervention time points for a given dichotomous variable [42, 43].$$\mathrm N=\left\{{\mathrm p}_1\;\left(100-{\mathrm p}_1\right)+{\mathrm p}_2\;\left(100-{\mathrm p}_2\right)\right\}\times{\mathrm f}_{\left(\mathrm\alpha,\mathrm\beta\right)}/\left({\mathrm p}_1-{\mathrm p}_2\right)^2$$

Where;$$\mathrm{N}=\text{Minimum sample size required for each group}$$$$\begin{aligned} \alpha=\:&\text{The level of significance used for detecting} \\& \text{an intervention difference}\:(0.05) \end{aligned}$$$$\begin{aligned} 1- \beta=\:&\text{The degree of certainty (power) that the difference p1-p2}, \\&\text{if present would be detected, often set at 0.8 (0.2)} \end{aligned}$$

$$f=\text{A function of}\ \alpha\ \mathrm{and}\ \beta\ \mathrm{when}\ \alpha\ \text{is 0.05 and}\ \beta\ \text{is 0.02 (7.9)}$$
$$\begin{aligned} \mathrm{P}_1=\:&\text{Expected percentage of an outcome variable}\\& \text{at the baseline of the intervention} \end{aligned}$$
$$\begin{aligned} \mathrm{P}_2=\:&\text{Expected percentage of an outcome variable} \\&\text{at the end of intervention} \end{aligned}$$

Previous interventional studies on fermented food have shown that host nutritional status, health and immune parameters are predominantly affected by the change in host gut microbiome [42–45]. Therefore, change of gut microbiome composition was used for sample size calculation. Previous studies have used the percentage presence of selected taxonomic groups of microbiota to interpret the gut microbiome changes [7, 46, 47]. Therefore, P1 and P2 in this study were derived based on a 17-week randomized controlled intervention study (*n* = 18, healthy adults) on high fiber food-based diet where percentage presence of *Oscillospira* at baseline was 31% and at the end of the intervention was 73% [7].

Therefore;

P_1_ = Expected percentage presence of Oscillospira at T_1_ = 31% [7] P_2_ = Expected percentage presence of Oscillospira at T_2_ = 73% [7]

The sample size obtained (*n* = 18.41) was corrected to account for design effect due to clustering (d). In most interventional studies, the maximum d has been reported as 2, and therefore the design effect was considered as 2 for this trial [48, 49]. Therefore, after correction, the sample size was 36.82. With another 25% non-response added, the final sample size was 45 participants.

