### Statistical analysis

Data will be analysed using the statistical package for the for the Social Sciences (SPSS) version 21.0. The changes in nutritional, health and immune parameters between the baseline (T_0_) and at the end of control phase (T_1_) will be analysed first to identify any significant change with time. The end point of control phase will serve as the pre-intervention point for further assessments. The changes in outcomes between the pre-intervention point (T_1_) and at the end of intervention phase (T_2_) will be analysed to determine any significant effects of *diyabath* consumption on the study group.

Paired t-test will be performed to determine the significance of the mean difference of pre- and post- measurements during the intervention phase. *P* value less than 0.05 is considered statistically significant.$$\begin{aligned} {\mathrm H}_0=\:&\left[\mathrm{Pre}-\mathrm{intervention}\;\mathrm{measurements} -\mathrm{post}\right. \left.-\:\mathrm{intervention}\;\mathrm{measurements}\right]=0 \end{aligned}$$

The same analysis will be performed in relation to the control phase. This evaluation is important to reveal any possible change in parameters that can occur due to seasonal, physiological or climatic changes in individuals.

Further, independent sample t-test will be performed to assess the significance between the intervention and control phases, in relation to the mean change in pre- and post-measurements observed during the intervention and control phases.$$\begin{aligned} {\mathrm H}_0=\:&\left[\mathrm{Mean}\;\mathrm{change}\;\mathrm{in}\;\mathrm{control}\;\mathrm{phase} \right. \left. -\:\mathrm{Mean}\;\mathrm{change}\;\mathrm{in}\;\mathrm{intervention}\;\mathrm{phase}\right]=0 \end{aligned}$$

Bioinformatics analysis of metagenomics of microorganisms evaluated from stool samples will be carried out based on16S amplicon sequence variants (ASVs) model.

Analysis of the effect of diyabath on primary outcomes will be based on modified intention-to-treat (mITT) and per-protocol (PP) principles. The mITT population will include participants who completed the first 15 weeks of the study period which covers the control phase and half of the intervention phase. The PP population will include the participants who completely adhered to the study protocol [53]. Missing data will be adjusted with multiple imputation.

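### The final sample size of 45 does not cover the stated 25% non-response: 36.82 needs 47 by addition or 50 to withstand that loss, and 45 leaves about 34

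*Protocol article*

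**What the plan says.** The Sample size section uses a formula for comparing two percentages. The inputs are "Expected percentage presence of Oscillospira at T_1_ = 31" percent and "Expected percentage presence of Oscillospira at T_2_ = 73" percent, with a multiplier f of 7.9. This gives n = 18.41. For clustering, "therefore the design effect was considered as 2 for this trial", and the result is given as: "Therefore, after correction, the sample size was 36.82". The last step reads: "With another 25% non-response added, the final sample size was 45 participants". The Abstract also gives 45 as the number of women in the trial.

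Other sections define how participants can be lost:
- **Discontinuation of the intervention:** voluntary withdrawal, antibiotics for 5 days or more, other fermented cooked rice-based food on more than 4 days, and supplement use decided case by case.
- **Compliance and drop-outs:** anyone who consumes 70% or less of the total dose counts as dropped out.
- **Statistical analysis:** the modified intention-to-treat set is limited to those who complete the first 15 weeks, the per-protocol set to those who adhere completely, and missing data are to be multiply imputed.

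**The concern.** The formula's result is defined in the section as a minimum, so each later step should protect it. The printed 45 is below what either usual way of allowing for 25% would give when applied to 36.82. A reader is told that the trial can lose a quarter of its participants and still have the number it needs, and that is not so.

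The allowance matters in this design. Participants must stay through a 10-week control phase before the intervention starts, and several rules remove them from the trial or from an analysis set. If losses reach the planned 25%, the evaluable number falls below the protocol's own requirement.

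**Working it through.** **Inputs, all from the Sample size section:** p1 = 31, p2 = 73, f = 7.9, design effect 2, allowance 25%, final N = 45. The value 7.9 fits a two-sided 0.05 test with 80% power (exact value 7.85). The section prints β as 0.02 beside it, but that β would give f of about 16.1, so 80% power is taken as intended.

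**Step 1: reproduce the base figure.**
N = {p1(100 − p1) + p2(100 − p2)} × f / (p1 − p2)²
= (31 × 69 + 73 × 27) × 7.9 / 42²
= 4110 × 7.9 / 1764 = 18.41. This agrees.

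**Step 2: design effect.** 18.41 × 2 = 36.82. This agrees.

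**Step 3: allowance for 25%.**

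| Method | Calculation | Result |
|---|---|---|
| Add 25% to the requirement | 36.82 × 1.25 = 46.03 | 47 rounded up |
| Keep the requirement after 25% loss | 36.82 / 0.75 = 49.09 | 50 rounded up |
| Truncate to 36, then add 25% | 36 × 1.25 = 45.0 | 45 |

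Only the third line gives the printed figure. It discards part of a stated minimum before inflating it.

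**Step 4: what 45 delivers.**
- Remaining after 25% loss: 45 × 0.75 = 33.75, about 34.
- Shortfall: (36.82 − 33.75) / 36.82 = 8.3%.
- Loss that 45 can absorb: 1 − 36.82/45 = 18.2%. In whole people, 37 must remain, so 8 of 45 may be lost (17.8%).
- By comparison, 50 × 0.75 = 37.5, which covers 36.82.

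**Step 5: effect on power**, by the same formula with the design effect kept. The effective n is the evaluable number divided by 2, and power = Φ(42 × √(n_eff/4110) − 1.96).
- At 36.82 evaluable: n_eff = 18.41, z = 0.85, power about 80%.
- At 33.75 evaluable: n_eff = 16.875, z = 0.73, power about 77%.

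**Step 6: detectable difference at 25% loss.** Solve the formula in Step 1 for p2 with N = 16.875 and p1 = 31. At p2 = 74.5, (2139 + 1899.75) × 7.9 / 43.5² = 16.86. The difference detectable with 80% power therefore rises from 42 to about 43.5 percentage points.

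**The case against.** There are four points on the other side.

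1. **The text says 25% was added, so the fair comparison is n × 1.25, not n/0.75.** On that reading the slip is one or two participants (46 or 47), with a traceable origin in rounding 36.82 down. This explains the figure. It does not rescue it, because 45 is still low on the additive reading, and addition does not protect a target against a 25% loss.

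2. **Non-response could mean refusals before enrolment.** The protocol gives no separate attrition rate, so reading the 25% as loss is an inference. But 45 is given as the number of women in the trial. If it were the number approached, enrolment would fall below 45, and nothing would be left for the losses that the protocol itself defines.

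3. **The modified intention-to-treat set and multiple imputation soften the loss.** This stands in part. A participant discontinued after week 15 can still be in that set, so the removal rules do not all reduce every analysis. Losses before week 15 do reduce it, and the per-protocol set is reduced by all of them.

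4. **The effect is small, and the target itself may be generous.** The power cost is about 3 points. The doubling for clustering is also open to question in a single hostel with simple random sampling. Without it, 33.75 evaluable would give about 97% power on the same formula. That limits the practical harm, but 36.82 is the requirement the protocol chose, and the allowance has to be consistent with it.

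**Conclusion.** The concern holds. The figure of 45 does not contain a 25% allowance on 36.82: 47 is needed by literal addition and 50 to withstand a 25% loss. As planned, 45 tolerates about 18% loss. If 25% are lost, about 34 remain, some 8% below the requirement, with power of about 77% instead of 80%.

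This assumes that the 25% applies to the 45 enrolled, that f = 7.9 and the design effect of 2 are kept as printed, and that those lost contribute nothing to the comparison. Where the modified intention-to-treat set retains late losses, the shortfall in that analysis is smaller. The error does not undermine the trial, but the stated figure is wrong as written and should be corrected.

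**What to change.** Keep 45 and correct the sentence on non-response. Suggested wording: *Forty-five participants allow for the loss of 8 (about 18%), leaving 37 evaluable against a requirement of 36.82. If 25% are lost, about 34 would be evaluable, giving about 77% power for 31% versus 73%, or 80% power for 31% versus about 74.5%.*

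If the 25% allowance is to stand, the sample size should read 50, here and in the Abstract.

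The first option costs one sentence and a slightly less favourable figure, with no further recruitment. The second means five more participants from a hostel that houses about 80 women on average.

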### Recruitment

The study setting has on average 80 women hostellers. The principle investigator (PI) will approach them through hostel authorities and will conduct an introductory session on the intervention procedure, potential risks and benefits of the study. Those who express interest will be given an information sheet in local languages (Sinhala and Tamil), with sufficient time to review the information and opportunities to ask questions and seek clarification from the investigation team. Using the hostel registry, potential candidates will then be identified using simple random sampling and screened for their eligibility for the study. This screening will include a clinical assessment including BMI performed by a medical officer who is not involved in the study. Relevant documents will be reviewed to confirm certain exclusion criteria. In addition, an interviewer-administered food frequency questionnaire (FFQ) validated for Sri Lankan adults will be administered to get a clear understanding of the participant’s usual dietary pattern [50]. Those already consuming *diyabath* or any other rice-based fermented food will be excluded from the study. Once eligibility is established based on the screening results, the potential candidates will be invited to participate in the study and informed written consent obtained by the PI.

### Implementation

Since this is a single-arm trial, there is no randomization into groups; and the same group of participants will be part of both the control and intervention phases with no specific mechanism for assigning or sequence concealment (Fig. 4 and Table 1).

**Fig. 4 Fig4:**
[figure not shown]
CONSORT flow chart for the trial

**Table 1 Tab1:** Participant timeline

Task	Study period (weeks)													
	**Recruitment**	**Non-intervention control period**						**Intervention period**					**Post-intervention follow up**	
ENROLLMENT - Eligibility screening - Informed consent	−2	0^a^	2	4	6	8	10^b^	12	14	16	18	20^b^	21	22^b^
	X													
	X													
Maintaining a food diary (24 h dietary records)		x	x	x	x	x	x	x	x	x	x	x	x	x
Baseline control assessment		x												
Anthropometry (height, weight, Waist circumference, Hip circumference, BMI)		x					x					x		x
Collection of blood samples (fasting) - serum micronutrients & serum ferritin - serum lipid profile - serum free fatty acids - AST, ALT - hsCRP, IL-6, IL-10, Cytokines - FBS & serum insulin		x					x					x		x
Collection of stool samples - Gut microbiome analysis (% abundance, alpha-diversity index, F/B ratio) - Short chain fatty acid profile		x					x					x		x

^a^assessment is done at the beginning of the week

^b^assessment is done at the last day of the week

Participants will be informed not to take part in any other nutritional intervention as well as not consume any nutritional supplementations including other cooked rice-based fermented foods during the study. A list of such food items will be given to them for reference at the beginning of the study. In addition, each participant will be asked to record daily all the foods that they have eaten other than what is provided by the hostel throughout the intervention phase. These records will be checked by an investigator during weekdays. Set reminders will be sent daily via SMS to all participants to keep records of their diets and will be asked to acknowledge the receipt of the message.

During the intervention period, every morning, the participants will be reminded via SMS to be present at the breakfast table. Standard portions of *diyabath* will be placed in the dining area before breakfast, ensuring uniformity in presentation across all participants. One investigator will be present at the site to observe the participants, to ensure that they consume *diyabath* as intended and answer any queries. The participants are requested to finish the served amounts and return the containers. If there is any leftover *diyabath*, the investigator will weigh it and make a record of it. This procedure will be repeated daily for 10 weeks during the intervention phase.

#### Discontinuation of the intervention

Participants of the study can voluntarily withdraw their consent and participation at any time during the study. In addition some participants would be compelled to take antibiotics or nutritional supplements during this period. In such instances, those who took antibiotics for 5 days or more will be discontinued. The discontinuation of those who started taking any nutritional supplement during the course of intervention will be considered case by case. Further, based on the dietary data records, participants who consumed other fermented cooked rice- based food for more than 4 days during the study period will be also discontinued from the study. In addition to that, participants will be discontinued from the study if they report any adverse events that may produce lethal outcomes.

#### Compliance and drop-outs

Based on the total amount of *diyabath* consumed throughout the intervention, as per the records, participants whose compliance with the consumption of *diyabath* is ≤ 70% of the total dose will be considered as dropped-out.

To enhance compliance, the participants will be briefed on the importance of continuing with the study and the potential health benefits. They will be informed that they will receive their test results with regards to biochemistry and body anthropometry, which will be an incentive to remain in the study.

### Data collection and storage

At the specified time points, anthropometric measurements will be taken by a trained assistant and blood samples drawn by an experienced nurse. Stools samples will be collected by the investigators and the gut microbiome analysis by a laboratory technical officer. All the outcome assessors will be blinded to the participants’ status. Due to the nature of this study neither trail participants nor the investigators will be blinded. All measurements will be based on standard methods followed using calibrated equipment.

#### Anthropometry

To minimise variability, each instrument will undergo the required calibration process, and all measurements taken by the same person (trained assistant) using the same equipment, as per the International Society for Advancement of Kineanthropometry (ISAK) protocol [51]. Measurements will be taken in duplicate at the same premises. If the mean of the two values exceeds a pre-determined threshold, a third measurement will be taken. Height will be measured in duplicate to the nearest 0.1 cm using a stadiometer (Seca 213, Seca gmbh & co); weight to the nearest 0.1 kg using a calibrated electronic scale (Seca 763); and waist and hip circumferences using a non-stretchable measuring tape (Seca 200). Body mass index (BMI) will be calculated as weight in kg/height^2^ in meters.

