### Study population

Women aged 20–35 years who have been residing in Colombo District for a minimum period of two years and with normal body mass index (BMI) (18.5 to 24.9kg/m^2^) will be recruited.

Pregnant and lactating women; those on long term medication for metabolic illnesses, severe concurrent infections, bowel disorders or intolerance to cereal based foods, coconut milk, red onion and dried chili (diagnosed following a clinical assessment made by a medical practitioner along with perusal of diagnosis cards, clinic records and treatment prescriptions for confirmation); women already consuming *diyabath* or any nutritional supplementation; or on antibiotics at the time of the study or within past two weeks will be excluded from the study.

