**Fig. 3 Fig3:**
[figure not shown]
Time structure of the trial

Primary outcomes of the study include changes in the following parameters:*Host gut microbiome composition:* Evaluated using percentage abundance of probiotic strains (i.e. *Lactobacillus* spp, *Bifidobacterium* spp) and other beneficial microorganisms (i.e. *Oscilllospira*, *Akkermansia muciniphila*), alpha-diversity index and firmicutes-to-bacteroidetes ratio (F/B). Diversity index reveals the change in the gut microbiome composition and is important to have a balanced ratio between the most common two phyla (Firmicutes and Bacteroidetes F/B) for homeostasis of the gut [38]. Gut microbiota is directly responsible to develop digestive, immunological and metabolic functions in host [39, 40].*Nutritional status and health parameters*: Evaluated by serum micronutrients and serum ferritin*Health biomarkers*: Assessed by lipid profile, high-sensitivity C-reactive protein (hsCRP), fasting blood sugar (FBS), aspartate aminotransferase (AST), alanine aminotransferase (ALT) and serum insulin*Immune markers:* Evaluated by analysing interleukin-6 (IL-6), IL-10 and cytokines

Each participant is expected to improve these parameters to either reach a healthy limit or a healthier end if already in the healthy limit.

Secondary outcomes of the study include:*Antioxidant capacity:* An increase in total antioxidant capacity in serum after consumption of an antioxidant rich food indicates absorption of antioxidants from the food and an enhanced in vivo defence status against oxidative stress [41].*Anthropometry:* Measured as waist circumference, hip circumference and BMI

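### The third anthropometric reading is triggered by the mean of the duplicate readings, which says nothing about whether they agree (minor, probably a slip for 'difference')

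*Protocol article*

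**What the plan says.** The Anthropometry section of the protocol article opens with its purpose: "To minimise variability, each instrument will undergo the required calibration process, and all measurements taken by the same person (trained assistant) using the same equipment". It cites the ISAK protocol as the standard for this. It then sets the number of routine readings, "Measurements will be taken in duplicate at the same premises", and the rule for adding one: "If the mean of the two values exceeds a pre-determined threshold, a third measurement will be taken".

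The article gives no value for the threshold. No other section restates the rule in terms of the difference between readings, and none gives a reason for repeating measurements in larger women.

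The Outcomes section lists anthropometry as a secondary outcome, "Measured as waist circumference, hip circumference and BMI". The participant timeline (Table 1) has these measurements taken at all four assessments.

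**The concern.** Duplicates are taken so that a misread or badly placed tape or scale shows up as a disagreement, and a third reading is meant to settle that disagreement. A trigger for the third reading therefore has to depend on how far apart the two readings are. The stated trigger depends on how large they are.

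What is at stake is the quality of the waist, hip and BMI data. Weight and height enter only through BMI and are not outcomes in their own right. The Statistical analysis section compares pre- and post-measurements within the same women, so a reading error that goes uncaught at one visit passes into that woman's change score.

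**Working it through.** **Inputs from the article.** Two routine readings per measure; a trigger on their mean; no threshold value; a stated aim of minimising variability; a target of 45 participants. The article states no figure that could be reproduced for this rule.

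**Step 1: what the mean can reveal.** Let the two readings be a and b, each the true value plus an independent error, with equal error variance. Then

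Cov((a + b)/2, a − b) = (Var a − Var b)/2 = 0.

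With normal errors, zero covariance means independence, so the mean is also independent of the absolute difference |a − b|. Knowing that the mean is above or below a cut-off does not change the chance that the pair is discordant.

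**Step 2: the two possible kinds of threshold.**
- *Repeat tolerance (for example 1 cm).* Any waist, hip or height in centimetres, and any weight in kilograms, has a mean far above this. The rule fires for everyone. Every pair is repeated, sound or not, and the check becomes a routine triplicate.
- *Body-size value (for example 80 cm for waist).* The rule fires for women whose mean is above it. A discordant pair with a mean below it is not repeated, and a concordant pair with a mean above it is.

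Neither kind separates discordant from concordant pairs.

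**Step 3: illustration.** The article gives no distribution, so every input here is an assumption: true waist mean 75 cm, between-woman SD 6 cm, reading-error SD 0.3, 0.5 or 1.0 cm, and 5% of pairs with a gross error of 3 cm, in either direction, in one reading. One million pairs were simulated for each reading-error SD.

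| Rule | Faulty pairs flagged | Sound pairs flagged |
|---|---|---|
| Mean above 70 cm | about 79% | about 80% |
| Mean above 75 cm | about 50% | about 50% |
| Mean above 80 cm | about 21% | about 20% |
| Mean above 1 cm | 100% | 100% |
| Absolute difference above 1 cm | 92% to 100% | 2% to 48% |
| Absolute difference above 2 cm | 76% to 99% | 0% to 16% |

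The ranges run over the three reading-error SDs, with the better performance at 0.3 cm. The simulated correlation between the mean and the absolute difference lay between −0.0002 and 0.0011, in line with Step 1.

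Two entries can be checked by hand at a reading-error SD of 1.0 cm:
- Mean above 80 cm, sound pairs: SD of the mean = √(36 + 1/2) = 6.04; (80 − 75)/6.04 = 0.83; upper tail about 20%.
- Difference above 2 cm, sound pairs: SD of the difference = √2 = 1.41; 2/1.41 = 1.41; two-sided tail about 16%.

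**Step 4: how much one missed error matters.** Under the same assumption, an uncaught 3 cm error in one of two readings moves that woman's visit value by 3/2 = 1.5 cm. It moves a mean over 45 women by 1.5/45 = 0.03 cm. Errors in either direction partly cancel, so the effect is mainly extra noise.

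**The case against.** The strongest reply is that this is a wording slip with little effect on conduct. The paragraph opens with the aim of minimising variability and cites an external measurement standard, and the Data collection and storage section says that standard methods will be used. The full protocol and the measurement form, neither of which is shown, may state the rule correctly. That is plausible, and it is a good reason to rate the point as minor. It does not remove the point: the trigger is not left out through condensing, it is stated, and stated on the wrong quantity. The absent threshold value and the absent rule for combining two or three readings are different. An article may leave those to the full document, and they are not part of this point.

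A reader might go further in three ways that the article does not support:
- *That the rule selects women by body size and makes precision depend on the value measured.* This follows only if the threshold is on the body-size scale. With a small tolerance everyone is measured three times, no discordant pair is left unrepeated, and the only cost is extra readings.
- *That the anthropometric comparisons are biased.* Nothing shows this. The comparison is within woman, with the same assessor, equipment and premises. Even under a body-size threshold, a woman well above or below it would tend to get the same number of readings at each visit.
- *That eligibility is affected.* Women "with normal body mass index (BMI) (18.5 to 24.9kg/m^2^) will be recruited", but the Recruitment section has screening BMI taken by a medical officer not involved in the study, and nothing says the duplicate rule applies there.

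**Conclusion.** The sentence is wrong as written. No choice of threshold lets a rule on the mean detect discordant duplicates, so the check cannot serve the paragraph's own aim. This rests on the algebra, which assumes independent reading errors of equal variance (and normality for full independence). It does not rest on the simulated percentages, which only illustrate it under assumed inputs.

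The severity is minor. The likely cause is a slip for 'difference'. The reach is limited to waist, hip and BMI as secondary outcomes. The primary outcomes and the sample size are untouched, and no distortion of the change scores has been demonstrated.

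**What to change.** In the Anthropometry section, change the trigger from the mean of the two values to the absolute difference between them, judged against the threshold pre-determined for that measure. Check that the measurement form and the assistant's instructions say the same.

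The cost is one sentence in the protocol and an edit to the form, with no extra staff or visits. If the form already uses the difference, only the published sentence needs correcting.
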